### Hypothesis Testing Criteria

A hypothesis is confirmed (regarded as statistically significant) if the lower boundary of the 95% confidence interval of its associated rate ratio exceeds one. The significance level is thereby set at .025.

If the first hypothesis is confirmed and the rate ratio of the second hypothesis exceeds one, then we will conclude that the first of the underlying hypotheses is supported by the data. If the second hypothesis is confirmed, then we will conclude that the second of the underlying hypotheses is supported by the data.

### Power Calculations

A 10-year follow-up (2001-2010), including all economically active men in Denmark aged 21-59 years in January 2001, yields ca. 420 cases of hospital treatment or death due to IHD per 100,000 person years, and 23 cases of death due to IHD per 100,000 person years. At baseline, 8.73% (112,699/1,291,665) of the workforce belonged to [name]’s group while 31.38% (405,385/1,291,665) belonged to the group “other blue-collar workers”. If we assume that the number of cases is proportional to the number of people in the various job groups, then the expected numbers of cases of hospital treatment or death due to IHD are approximately 4650 in [name]’s group and 16,000 among the other blue-collar workers. The corresponding numbers for death due to IHD are 255 and 880.

With the above data as input, the statistical powers of the tests are given as a function of the true rate ratio in Figure 1. The calculations are based on the Poisson distribution, the propagation of error formulas, and the central limit theorem.

**Figure 1 figure1:**
[figure not shown]
Approximate power curves for the hypothesis that the rate of IHD is higher among men in [name]’s group than it is among other blue-collar workers as a function of the true rate ratio (RR).

### Sensitivity Analysis 1

Since the latency period for ischemic heart disease is long [25], a person will be kept in his baseline exposure category throughout the follow-up regardless of whether or not he shifts to another job or retires from the labor market during the follow-up.

During the study period, the participants were eligible for an old age pension at the age of 65. It was, however, also possible to retire prematurely at the age of 60, according to an optional public insurance policy. It is possible that heavy lifting at work influences the propensity to opt for early retirement. It is also possible that early retirement influences the risk of IHD. Early retirement might, in other words, be a moderating factor for the risk of subsequent IHD as a function of heavy lifting at work, among people who are 60 years or older. If this is the case, then we might not be able to generalize the results of the present study to nations or time periods with other retirement schemes.

To shed some light on this issue, we will perform a sensitivity analysis where we censor the follow-up whenever a participant reaches age 60. The clinical endpoint of the sensitivity analysis will be hospital treatment or death due to IHD as principal diagnosis/cause of death.

### Sensitivity Analysis 2

The inclusion/exclusion criteria of the primary analysis are based solely on information from the calendar year preceding baseline. It would have been possible to involve information from more than one calendar year; however, since we want our estimates to be representative of the situation among all of the concerned workers who were healthy enough to be classified as economically active at baseline, we elected our exclusion criteria parsimoniously. In the primary analysis, we exclude all workers who were treated for IHD sometime during the calendar year preceding baseline and, by doing so, we have ascertained that an observed instance of hospital treatment during the follow-up is a new episode rather than a revisit in a course of treatment that had already started before baseline. We cannot know, however, if this was the first occurrence of the disease ever.

It is possible that some workers, due to ischemic heart disease, changed from an occupation that entails heavy lifting to an occupation that does not entail heavy lifting, a few years prior to baseline. If this is the case, then, from an etiological viewpoint, our estimates will be biased. We will address this issue with a sensitivity analysis that only includes those who lived in Denmark, were free from IHD-related hospital contacts, and belonged to the same occupational category throughout a 3-year period prior to baseline. The clinical endpoint will be hospital treatment or death due to IHD. Since our project does not have access to information about people who are younger than 20 years and the inclusion/exclusion criteria are based on a 3-year period, we can only include people who were at least 23 years old at baseline. In all other respects, we will use the design of the primary analysis.

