### Study Design

The study population consists of all male inhabitants of Denmark, who at baseline (January 1, 2001) were 21-59 years old and belonged to any of the two occupational groups given above. These people will be followed in our national registers, from January 1, 2001 to December 31, 2010. Approximately half a million working men will be included in the study.

The following clinical endpoints will be considered: (1) hospital treatment or death with IHD as principal diagnosis/cause of death (the case definition includes these ICD-10 codes: I20 angina pectoris, I21 acute myocardial infarction, I22 subsequent myocardial infarction, I23 certain current complications following acute myocardial infarction, I24 other acute ischemic heart diseases, I25 chronic ischemic heart disease), and (2) death with IHD as principal cause of death.

The study population will be followed, first for death or hospital treatment due to IHD and then for death due to IHD. Only those who were free from IHD-related hospital visits throughout the calendar year preceding baseline will be included in the analysis.

For each of the two endpoints, each of the included individuals will be followed until any of the following events occur: he reaches the clinical endpoint of the follow-up, he emigrates, he dies, or the study period ends. Person years at risk (PYRS) will be calculated for each individual.

We will use Poisson regression to estimate rate ratios between [name]’s blue-collar workers and all other blue-collar workers, while adjusting for age (10-year age groups). The rate ratios will be presented with 95% confidence intervals. PROC GENMOD in SAS version 9.3 will be used to implement the analysis.

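### Sensitivity Analysis 1 asks about effect modification from age 60 but plans only an RR before 60; the RR from 60 and its contrast with the earlier RR are not produced

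*Protocol article*

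**What the plan says.** The section Sensitivity Analysis 1 notes that premature retirement was possible from age 60. It suggests that early retirement might "be a moderating factor for the risk of subsequent IHD as a function of heavy lifting at work, among people who are 60 years or" above. The stated consequence is that "we might not be able to generalize the results of the present study to nations or time periods with other retirement schemes". The stated ambition is modest: "To shed some light on this issue", the authors write, "we will perform a sensitivity analysis where we censor the follow-up whenever a participant reaches age 60". The endpoint is the combined one: "The clinical endpoint of the sensitivity analysis will be hospital treatment or death due to IHD as principal diagnosis/cause of death". The same section keeps each man in his baseline exposure category throughout follow-up.

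Under Study Design, the cohort is men "who at baseline (January 1, 2001) were 21-59 years old", followed "from January 1, 2001 to December 31, 2010". The Poisson model compares the two occupational groups "while adjusting for age (10-year age groups"). The text does not say whether these are groups of baseline or attained age, or where they are cut. Hypothesis Testing Criteria covers hypotheses 1 and 2 only.

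**The concern.** A question about moderation from age 60 asks whether the RR in that age range differs from the RR before it. The planned analysis removes all person-time from 60 onward. It returns one side of that comparison and leaves out the side in which the moderation is suspected.

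The article names no other estimate to set it against, so the natural companion is the primary RR. The primary analysis contains every event before 60, so the two RRs are nested and their gap understates the difference between the age ranges. No contrast or interval is planned that would show its full size and uncertainty. What is at stake is the later statement on generalisability to other retirement schemes, not the tests of the two hypotheses.

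**Working it through.** **Inputs from the protocol (Power Calculations).** Expected combined-endpoint cases: about 4650 in the heavy-lifting group and 16,000 among other blue-collar workers. Group sizes: 112,699 and 405,385. Rate: 420 per 100,000 person-years.

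**Reproducing those counts.** Cases = men × mean follow-up × rate.
- 10 years: 112,699 × 10 × 0.0042 = 4733 and 405,385 × 10 × 0.0042 = 17,026.
- 9.8 years: 4639 and 16,686.

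The first count reproduces within 2%. The second is 4 to 6% below proportional allocation. That is a separate matter with no bearing here: the SE of the overall log RR is √(1/4650 + 1/16,000) = 0.0167 with the stated counts and 0.0164 with 4733 and 17,026. The stated counts are used below.

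**Assumed input: f, the share of events at age 60 or older.** The documents do not give it. Only men aged 50-59 at baseline can contribute person-time from 60. With baseline ages spread evenly over 21-59 and 10 full years of follow-up, about 13% of person-time falls at 60 or over. If the IHD rate rises 1.5- to 3-fold per decade of age, f is about 0.24 to 0.46. The range used is 0.2 to 0.5, with the same split of cases between the groups in both age ranges.

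**What the planned pair of RRs would show.** To a good approximation,

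log RR(all) = (1 − f) · log RR(<60) + f · log RR(≥60),

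so log[RR(<60) / RR(all)] = f · log[RR(<60) / RR(≥60)].

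**What a direct contrast would give.**

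SE(log ratio) = √[1/(4650(1−f)) + 1/(16,000(1−f)) + 1/(4650f) + 1/(16,000f)].

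The ratio detectable with 80% power (two-sided 5%) is exp[(1.96 + 0.8416) · SE]. Power is Φ(|log ratio| / SE − 1.96).

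Illustration 1, RR 1.10 before 60 and 1.00 from 60 (true ratio 1.10):

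| f | Primary RR | Visible ratio, censored / primary | SE of log ratio | Detectable ratio, 80% power | Power of direct contrast |
|---|---|---|---|---|---|
| 0.2 | 1.079 | 1.019 | 0.042 | 1.12 | 0.63 |
| 0.3 | 1.069 | 1.029 | 0.036 | 1.11 | 0.75 |
| 0.4 | 1.059 | 1.039 | 0.034 | 1.10 | 0.80 |
| 0.5 | 1.049 | 1.049 | 0.033 | 1.10 | 0.82 |

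Illustration 2, RR 1.15 before 60 and 1.00 from 60 (true ratio 1.15): the primary RR is 1.118, 1.103, 1.087 and 1.072. The visible ratio is 1.028, 1.043, 1.057 and 1.072, and the power of the direct contrast is 0.92, 0.97, 0.98 and 0.99.

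**Is information lost?** Take f = 0.3 and RR 1.10 against 1.00.
- Nested difference: 0.3 × log 1.10 = 0.0286. Its SE, allowing for the shared events, is √(Var(<60) − Var(all)) = √(0.0199² − 0.0167²), which is 0.0109 from unrounded values. z = 2.6.
- Direct contrast: 0.0953 / 0.0364, z = 2.6.

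The two are equivalent. The dilution is in what is displayed, not in what the data can tell.

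**The case against.** The best defence is that the censored analysis answers the worry as worded. The worry is generalisability to other retirement schemes. An RR from person-time before 60 is largely untouched by the early-retirement scheme, so it is a legitimate robustness estimate. This stands, and it is why the analysis should be kept. It does not show whether the association changes from 60, which is the reason the section gives for the worry.

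Three stronger readings are tempting, and the documents do not support them.
- **That the nested comparison has less power, or that overlapping intervals would show no difference.** The equal z-values refute the first. Overlap of two intervals is not a valid gauge for nested estimates.
- **That the protocol means to compare the RRs by eye and conclude there is no difference.** It states neither. How a sensitivity RR is set beside the primary one may also be left to a fuller plan, although Study Protocol in the Discussion describes models and test criteria as completely defined in advance.
- **That the confirmatory result is at risk.** No decision rests on this analysis. Even in the most diluted row of illustration 1 (primary RR 1.049), the lower 95% limit is about 1.015, so hypothesis 1 would still be confirmed.

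A further objection concerns the remedy, and it stands. Person-time from 60 comes only from men aged 50-59 at baseline and lies later in their follow-up. A contrast at 60 therefore mixes retirement with attained age, birth cohort and time since baseline exposure.

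**Conclusion.** The point holds as an improvement to an exploratory check, not as an error. Sensitivity Analysis 1 raises moderation from age 60 and delivers a valid RR before 60, but neither the RR from 60 nor the contrast between the two. Placed beside the primary RR, the planned estimate shows only 20 to 50% of the log difference under the assumed f. Some dilution follows for any f below 1; its size depends on f, and the RR pairs of 1.10 or 1.15 against 1.00 are illustrations. With the protocol's own expected case numbers, a direct contrast would be precise enough to be useful.

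**What to change.** Keep the censored analysis and add the following to the section:
- Split each man's person-time at his 60th birthday, using attained-age groups that break at 60. Follow-up ends before age 70 (under 60 at baseline plus 10 years), so one 60-69 group covers all the later time.
- Add a group × (<60 / ≥60) term to the Poisson model for the combined endpoint. Report the RR before 60, the RR from 60, and their ratio with a 95% CI.
- State that the contrast is exploratory. A difference at 60 could also reflect attained age, birth cohort or time since baseline exposure, so it does not by itself show a retirement effect.

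The age-group definition matters. The RR before 60 from the joint model equals the one from the censored analysis only if both use the same attained-age groups with a break at 60. Baseline-age groups, or a band such as 51-60, would give a different figure.

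The cost is a few sentences of protocol text, slightly more analysis work and one extra exploratory contrast to interpret. No new data are needed and the tests of hypotheses 1 and 2 keep their criteria.

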## Discussion

### Study Protocol

With this study protocol, we define the hypotheses, inclusion criteria, statistical models, and test criteria completely before we look at any relationship between the exposure and outcome variables in our data. By doing so, we have eliminated hindsight bias. The prospective design and the exclusion of prevalent cases ascertain that the exposure takes place before the outcome. The size of the study gives us a tremendous statistical precision and, since we are dealing with registers that cover the entire population of Denmark, we do not have any problems with sampling bias, response bias, or volunteer bias.

### Challenges

The drawback of the study is that it lacks individual-based data on some quite important predictors for IHD, such as smoking [26], BMI [27], physical fitness [28], blood pressure, and cholesterol [29]. It is well documented that the distribution of risk factors for IHD differs between social groups [30,31] and that the rates of IHD generally are lower among white-collar workers compared with blue-collar workers. To mitigate the possible influence from uncontrolled risk factors, we decided to only include blue-collar workers in our comparison group. The drawback of this decision is that the comparison group also, to some degree, will contain elements of heavy lifting.

We used data from a survey on a random sample of the study population to look at differences, between the group associated with heavy lifting and other blue-collar workers, in the prevalence of smoking, overweight, obesity, exposure to noise, poor decision latitude, high job insecurity, prolonged working hours, and shift work. We did not find any difference in smoking prevalence but we found that the prevalences of overweight, prolonged working hours, and shift work were statistically significantly lower among people in the group associated with heavy lifting than they were in the comparison group. These differences are likely to bias our estimate slightly in the opposite direction of the hypothesis, which decreases the probability of a false positive finding.

Another aspect of the study that needs to be considered is the possibility of detection or referral bias. The perceived adverse effects of a heart condition might increase with heavy lifting activities. Hence, the probability of becoming aware of and the propensity to seek medical treatment for a minor IHD might be higher among people who are exposed to heavy lifting at work than it is among other blue-collar workers. This potential source of bias points in the same direction as our hypothesis and would thereby increase the probability of a false positive finding. The probability that referral bias causes us to erroneously conclude that the data support the first of our underlying hypotheses is, however, decreased by our testing criteria, which tell us that we only are allowed to draw such a conclusion if also the rate ratio of death due to IHD is greater than one.

## Abbreviations

BMI: body mass index
DISCO-88: Denmark International Standard Classification of Occupations
DWECS: Danish work environment cohort survey
ICD-10: International Classification of Diseases, 10th revision
IHD: ischemic heart disease
NRCWE: National Research Centre for the Working Environment
RR: rate ratio
